Response was associated with a microbial composition shift towards the donor’s profile, including increase of alpha-diversity and restoration of *Clostridium* clusters IV, XIVa and XVIII, which belong to the *Firmicutes* (currently renamed to *Bacillota*) phylum.^13^ Sustained remission (⩾1 year) was linked to known butyrate-producing bacteria and overall increased butyrate production capacity, as assessed through functional predictions and targeted quantitative PCR (qPCR).^13^ Butyrate, a short chain fatty acid (SCFA),^14^ is primarily produced by species within the Firmicutes phylum (currently renamed to *Bacillota*)^15^ and is known to downregulate proinflammatory responses in intestinal epithelial cells and to support the gut barrier function.^14^ In contrast, non-response and relapse were associated with increased levels of *Proteobacteria* (currently renamed to *Pseudomonadota*) in patients’ baseline samples and high levels of bacteria that are phylogenetically related to the mucus degrader *Ruminococcus gnavus*^16^ in donors.

Three subsequent published RCTs^10^,^12^ reported a significant treatment effect of FMT ranging between 24 and 32%, compared with placebo rates of 5 to 9%. FMT protocols varied greatly regarding the number of infusions, route of administration, single vs multidonor approach and processing techniques. Microbiota analysis of these trials showed an association of response with several factors, including Clostridium cluster IV, XVII and potential butyrate-producing bacteria,^11 12^ similar to the TURN trial results. Remarkably, a Canadian trial by Moayyedi *et al*,^12^ revealed a highly efficacious donor responsible for seven out of nine responders, suggesting a donor-dependent effect. This donor was particularly rich in *Lachnospiraceae* and *Ruminococcus*.

The majority of the gut microbiota consists of oxygen-sensitive bacteria,^17^ under which butyrate producers. Therefore, regular applied aerobic processing techniques of donor stool diminish the bacterial viability of obligate anaerobes compared with strict anoxic processing, as recently published by our group.^18^ An Australian trial by Costello *et al*^10^ used anoxic processing and reported that the bacteria most strongly associated with clinical response were obligate anaerobes.^10^

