### Trial design

The TURN2 trial is a randomised, double-blind, placebo-controlled, multi-centre, parallel-group phase 2 trial with open-label extension option for non-responders in the placebo arm. Eligible patients will be randomised to receive anoxic donor FMT or anoxic autologous FMT in a 1:1 allocation ratio.

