#### Investigational product

Donor faeces is collected (minimum 20 grams) in an allocated toilet in the Amsterdam UMC in a plastic container placed in a vacuum box (10006101;0 from ALLPAX). Immediately after donation, AnaeroGen sachets (Anaerogen Compact, Thermo Fisher) are added as oxygen scavenger and the container is evacuated to a 97% vacuum. The donation is then transferred to an anaerobic chamber (Anaerobic workstation Concept 500, Baker Ruskin) within 30 min for further processing. This collection and transfer protocol was adjusted from An *et al*,^29^ who demonstrated that their approach facilitated the survival of obligate anaerobes using propidium monoazide (PMA) and culturing. Inside the anaerobic chamber, the stool is weighed and homogenised with NaCl 0.9% in a ratio of 1:3.3–5.5 (depending on consistency) using a blender with a steel autoclavable container (Warring 1LB20ESA). The solution is then filtered using a metal autoclavable tunnel and gauze. Cryoprotectant glycerol (85%) is added to achieve a final concentration of 10%. The prepared FMT is stored in labelled syringes covered with aluminium foil in a −70°C freezer. Before use, syringes are thawed in an anoxic box (AnaeroPack 7.0L, Mitsubishi) with AnaeroGen sachets for either 5 hours at room temperature or overnight in a refrigerator. Patients receive FMT from the same donor for each treatment, while multiple donors are employed throughout the study.

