### Sample size calculation

At the time of writing the initial protocol, four RCTs^9^,^12^ had been published on FMT for inducing remission in UC, including our previous FMT trial (TURN).^9^ In the TURN trial, the primary endpoint was reached in 30% of patients, with a placebo response rate of 20%.^9^ The other three published RCTs had efficacy rates ranging from 24 to 32% and placebo rates from 5% to 9%.^9^,^12^ In the current study, we aim to augment the treatment effect by selecting faeces donors on their microbiota profile, using anoxic processing, and by promoting engraftment through dual-route administration and repeated FMTs. We therewith estimate to boost the treatment effect to 33–40%. By using a more stringent endpoint, we anticipate a lower placebo compared with the TURN trial, aligning with rates observed in other studies.

The sample size calculation was performed using nQuery software (Cork, Ireland) with the following assumptions: efficacy in the placebo group of 10%, efficacy in the treatment group of 37%, two-sided significance level (α) of 0.05 and desired power of 80% (β=0.20). Based on these parameters, a sample size of 38 patients per group, totalling 76 patients, is required. The study incorporates an adaptive design that allows for an increase in the sample size up to a maximum of 100 patients to account for (early) drop-outs (online supplemental table 6).

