### Patient allocation and blinding

Randomisation is performed using a computerised random-number generator within the Electronic Data Capture system Castor, allocating patients in a 1:1 ratio to either allogenic (donor) FMT or autologous FMT. Randomly permuted blocks of 2, 4 or 6 are applied with no additional stratification. A research assistant conducts the randomisation and subsequently prepares autologous FMT or collects syringes with donor FMT (based on Epstein-Barr virus and Cytomegalovirus matching), according to the allocation outcome.

To ensure blinding, FMT syringes are visually and olfactorily concealed in capped syringes covered with aluminium foil and labelled identically for autologous and donor FMT. All labels include a tearable section with the allocation and a unique code. A second independent research assistant verifies either the preparation of autologous FMT or the correct matching of donor syringes and removes the tearable labels, which are maintained in a drug accountability log. The research assistants are the only individuals who are unblinded and have no further role during the study. FMT administration and all visits are conducted by a blinded research nurse or fellow. Gastroenterologists performing sigmoidoscopies and treating physicians are also blinded.

De-blinding of investigators may occur after all patients have reached the primary endpoint (week 8), to facilitate data publication. Patients who do not meet the secondary endpoint of clinical response at week 8 and who have an endoscopic Mayo subscore of ≥2 at week 8 can be unblinded if they wish to continue with open-label extension. Open-label extension with donor FMT will only be available to patients who were originally allocated to autologous FMT.

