### Statistical methods

Primary and secondary outcomes will be analysed using a ‘modified intention-to-treat’ design, meaning that data from all randomised patients will be analysed, with the exception of data of those who did not receive any FMT treatment (ie, patients who dropped out before V3). For the primary endpoint, the analysis will use a conservative approach in which participants with missing week 8 outcome data are classified as not in remission, irrespective of reason for missingness. To correct for missing data due to drop-outs, additional randomisation will be performed according to a fixed schedule outlined in online supplemental table 6.

Demographic data will be reported as either the mean with a 95% CI, or as the median and IQR for data not normally distributed. Analysis of the primary endpoint will be will be calculated using a two-sided χ^2^ test. Descriptive and exploratory data analysis will be reported as per the described primary and secondary endpoints. Statistical significance will be established at p<0.05 with a CI of 95%. P values of secondary outcomes will be adjusted using the Holm-Bonferroni procedure to account for multiple testing. Statistical analyses will be conducted using SPSS V.29.0 software (Chicago, IL) or R programming language version 4.

To identify dietary patterns assessed with the GINQ, principal component analyses will be performed on 22 food groups. Flare occurrence after FMT will be analysed using multivariable Cox proportional hazards models. To identify microbial candidates that are associated with response to FMT, we will perform differential abundance analysis comparing responders versus non-responders using linear regression analyses considering age, sex, BMI, proton pump inhibitor use, antibiotic and sequencing read depth as covariates. Next, we will analyse data derived from the longitudinal monitoring to detect changes after FMT and donor-derived engraftment of species associated with (non)-response.

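### The unadjusted χ² primary test is valid but gives up a little precision by leaving out recorded baseline severity and steroid use, and its interval may be too narrow if donors are shared, differ in effect, and the result is meant to reach beyond them

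*Protocol article*

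**What the plan says.** Statistical methods fixes the primary test: "Analysis of the primary endpoint will be will be calculated using a two-sided" χ² test. A 95% confidence level is given without an interval method. Covariates appear in that section only for the exploratory microbial regression, and neither disease severity nor donor is among those listed.

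Patient allocation and blinding adds that "Randomly permuted blocks of 2, 4 or 6 are applied with no additional stratification".

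The eligibility criteria show what is known at entry: partial and full Mayo scores, the endoscopic subscore, and use of prednisone or budesonide. A baseline adapted Mayo score must also exist, because the secondary response outcome is a fall from it.

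On donors, Investigational product states: "Patients receive FMT from the same donor for each treatment, while multiple donors are employed throughout the study". The Introduction reports that an earlier trial "revealed a highly efficacious donor responsible for seven out of nine responders, suggesting a donor-dependent effect". The Discussion says that donor dependence has been seen in several trials, and donors are ranked and selected on that premise.

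The sample-size section assumes "efficacy in the placebo group of 10%, efficacy in the treatment group of 37"%, with "two-sided significance level (α) of 0.05 and desired power of 80% (β=0.20"), and concludes that "a sample size of 38 patients per group, totalling 76 patients, is required". It makes no allowance for donors.

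**The concern.** There are two separate issues.

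**Baseline covariates.** With 76 patients and no stratification, chance imbalance in severity or steroid use is neither limited by design nor handled in the analysis. Steroid use bears directly on a steroid-free endpoint. The Discussion also cites high disease severity as one suggested reason for another trial's lack of effect. Information already collected goes unused.

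**Donor clustering.** If several patients receive one donor's product and donors differ in effect, outcomes in the donor arm are correlated while those in the autologous arm are not. A test and interval built on independent patients then leave between-donor variation out of the stated uncertainty. This matters if the result is read as describing donors selected in this way in general, and not only the donors who took part.

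**Working it through.** **1. Reproducing the plan's figure.** Inputs from Sample size calculation and Trial design: p₀ = 0.10, p₁ = 0.37, two-sided α = 0.05, power 80%, 1:1 allocation. The pooled rate is p̄ = 0.235.

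n = [1.96·√(2·0.235·0.765) + 0.8416·√(0.10·0.90 + 0.37·0.63)]² / 0.27²
= (1.1753 + 0.4784)² / 0.0729 = 37.5, so 38 per arm.

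Power at 38 per arm is 80.5% by this formula and 82.3% by exact enumeration of the uncorrected χ². The continuity-corrected formula would need 45 per arm. The plan was therefore sized for an uncorrected χ² with independent patients and no covariate, and the stated test agrees with that.

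**2. What covariate adjustment would add.** The article gives no prognostic strength. The simulation used one standard-normal baseline covariate, held the marginal rates at 10% and 37%, and compared χ² with an adjusted logistic score test (6,000 runs each).

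| Odds ratio per SD (assumed) | χ² power | Adjusted power | Gain (points) |
|---|---|---|---|
| 1.5 | 82.0% | 83.0% | 1.0 |
| 2 | 82.6% | 85.0% | 2.4 |
| 3 | 83.0% | 88.5% | 5.5 |

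The model size is limited by events: 38 × 0.10 + 38 × 0.37 = 3.8 + 14.1, or about 18 expected remissions, only about 4 of them autologous.

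**3. What donor clustering could do to the interval.** Donor count, recipients per donor and ICC are not in the article, so each row below is an assumption. With D donors, m = 38/D recipients each, and the design effect DE = 1 + (m − 1)·ICC applies to the donor arm only.

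Naive SE = √[(0.0900 + 0.2331)/38] = 0.0922, half-width 1.96 × 0.0922 = 18.1 points.
Clustered SE = √[(0.0900 + 0.2331·DE)/38].

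Example with 4 donors and ICC 0.20: m = 9.5, DE = 1 + 8.5 × 0.20 = 2.70, SE = √[(0.0900 + 0.6294)/38] = 0.1376, which is 1.49 times the naive SE.

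| Donors, ICC | DE | True SE / naive SE | Half-width (points) | Simulated coverage of naive 95% interval | Power of a test allowing for clustering |
|---|---|---|---|---|---|
| ICC about 0 | 1.00 | 1.00 | 18.1 | 94.2% | 80.5% |
| 15, 0.02 | 1.03 | 1.01 | 18.3 | 93.8% | 79.8% |
| 10, 0.05 | 1.14 | 1.05 | 19.0 | 92.8% | 77.4% |
| 6, 0.10 | 1.53 | 1.18 | 21.3 | 88.8% | 69.5% |
| 4, 0.10 | 1.85 | 1.27 | 23.0 | 85.9% | 64.1% |
| 4, 0.20 | 2.70 | 1.49 | 27.0 | 78.2% | 53.1% |

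Coverage comes from a beta-binomial simulation (200,000 runs per cell) of a Wald interval. The Wald form is also an assumption, since no interval method is stated.

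**The case against.** The case for leaving the plan alone is substantial, and much of it stands.

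- **The χ² test is valid.** Under "anoxic donor FMT or anoxic autologous FMT in a 1:1 allocation ratio" by randomisation, an unadjusted comparison needs no covariates to be correct. A reader might infer that omitting severity is a mistake in the plan. The documents do not support that. It costs efficiency only.
- **The gain may be small.** Entry is restricted to full Mayo 5–9 and an endoscopic score of at least 2, which narrows the range of severity. A reader might inflate the sample by 1/(1 − R²) and obtain 82.5% power at R² = 0.05 up to 88.6% at 0.20. That is a linear-model formula with an R² the article does not give, so the simulated 1 to 6 points is the better guide.
- **A reader might infer that the intervals are too narrow outright.** The article does not establish that. It does not say how many patients share a donor, or that the result is meant for a wider population of donors. It describes a phase 2 trial and limits its own generalisability. For the donors actually used, an independent-patient analysis is about right. Selecting the top-ranked half of donors on common criteria may also reduce the differences between them.
- **A reader might infer an inflated false-positive rate.** Simulated χ² error at a 20% rate is 8.3% with 6 donors and ICC 0.10. But this requires donors who differ while their average effect is exactly nil, so that some do worse than autologous treatment. If donor FMT does nothing for anyone, donors cannot differ in effect, and the error at that rate is 5.0%.
- **Donors are not randomised.** They are matched to recipients on Epstein-Barr virus and cytomegalovirus status, and each donates for at most 12 weeks. Remission by donor is therefore mixed with serostatus and possibly calendar time.
- **An analysis plan that is not shown may already contain supportive analyses.**

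Two things remain. The article does commit to a primary test that uses none of the recorded baseline information. Its own rationale is that donors differ in effect, and it looks ahead to donor-recipient matching, which makes between-donor variation relevant to interpretation.

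**Conclusion.** The point holds in a limited form. The primary test is valid and consistent with the 38 per arm. Leaving out baseline severity and steroid use gives up about 1 to 6 points of power if the covariate's odds ratio is 1.5 to 3 per SD. This is an assumed range for a single continuous covariate, and a yes/no steroid variable may behave differently.

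The donor issue depends on three conditions together: donors are shared, the ICC is above zero, and inference goes beyond the donors used. Under those conditions the true SE is between 1% and 49% larger than the naive SE over the assumed scenarios, which runs from negligible to serious. The article cannot narrow that range. This supports an additional analysis and fuller reporting. It does not show that the planned test is wrong.

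The two remedies move power in opposite directions: adjustment raises it, and allowing for donors lowers it (to between 79.8% and 53.1% in the table). For that reason the donor analysis belongs in a supportive role.

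**What to change.** 1. **If investigators are still blinded,** prespecify logistic regression of the primary endpoint on arm, baseline adapted Mayo score and baseline steroid use (yes/no). Report it as a standardised risk difference with a 95% CI. Use no more than these two covariates, given about 18 expected remissions. Keep the uncorrected Pearson χ², the test the trial was sized for, as supportive.
2. **If unblinding has already happened,** keep χ² as primary and label the adjusted analysis supportive. The timing needs checking: the article reports that recruitment ended in November 2024 and allows unblinding once all patients have reached week 8.
3. **In either case,** add a supportive analysis with clustering in the donor arm only, by donor random intercept or donor-robust interval. Report the number of donors, recipients per donor and remission by donor. State that donors were matched on viral status and not randomly assigned, so differences by donor are descriptive.

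The lack of stratification cannot be changed now.

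The cost is a few sentences of analysis text and a little code. The donor analysis will have a wider and less stable interval, especially with few donors. The adjusted model may be unstable with about four autologous remissions, so a fallback for non-convergence should be named in advance.

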#### Secondary outcomes

Secondary outcomes include:

Proportion of patients with:Clinical response per adapted Mayo score at week 8 (ie, excluding Physician’s Global Assessment (PGA) subscore): a decrease from baseline ≥2 points and ≥30%, plus a decrease in RBS≥1 or an absolute RBS≤1.Clinical improvement per partial adapted Mayo score at week 8 (ie, excluding PGA and endoscopy subscore): a decrease from baseline ≥1 points and ≥30%, plus a decrease in RBS≥1 or an absolute RBS≤1.Full clinical remission per full Mayo score at week 8: a decrease from baseline of ≤2 points with no subscore >1.Complete remission per full Mayo score at week 8: ≤2 points reduction from baseline with no subscore >1 and a rectal bleeding score and endoscopic subscore of 0.Sustained steroid-free remission per adapted Mayo at week 8; SFS≤1, RBS=0, endoscopic subscore≤1 and no need for rescue therapy until week 52.Endoscopic complete remission at week 8: endoscopic subscore=0.Endoscopic improvement at week 8: endoscopic subscore of 0 or 1.Endoscopic response at week 8: ≥1 point reduction in summed endoscopic Mayo score (endoscopic subscore of rectum+endoscopic subscore of sigmoid).Histological remission assessed via Nancy Histological Index (NHI)^32^,^34^: NHI≤1.Change in:Simple Clinical Colitis Activity Index from baseline to week 1, 2, 3, 4, 8, 18, 39 and 52.Partial Mayo: from baseline to week 1, 2, 3, 4, 8, 18, 39 and 52.IBD-Control: from baseline to week 2, 4, 8, 18, 39 and 52.Occurrence of AEs

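### The Holm-Bonferroni rule has no boundary: it takes in adverse events and up to 22 instrument-visits, so the family is anywhere from 13 to 32 tests and any adverse-event p value would be adjusted

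*Protocol article*

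**What the plan says.** The Statistical methods section sets the level, "Statistical significance will be established at p<0.05 with a CI of 95"%, and then the multiplicity rule: "P values of secondary outcomes will be adjusted using the Holm-Bonferroni procedure to account for multiple testing". No subset, order, time point or safety exemption is named.

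The Secondary outcomes section holds three kinds of item under one heading:
- nine proportions, beginning with "Clinical response per adapted Mayo score at week 8";
- change scores for SCCAI (8 visits), partial Mayo (8 visits) and IBD-Control (6 visits), running from the treatment weeks to week 52;
- last, "Occurrence of AEs".

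The Patient allocation and blinding section lets patients without clinical response at week 8, and with an endoscopic subscore of 2 or more, be unblinded. Those from the autologous arm may then receive donor FMT open label.

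**The concern.** Multiplicity adjustment protects against false claims of benefit. Applied to harms it works the other way, because it makes a real excess more likely to be labelled non-significant. Safety stands beside efficacy in the trial's stated objective, so an adverse-event comparison in the final report matters.

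The second issue is the size of the family. Holm thresholds depend on the number of tests. If every visit of every score counts, the hurdle for endoscopic improvement or histological remission is set mostly by repeated visits. Nine of those visits fall at weeks 18, 39 and 52, when some autologous patients may already have received donor FMT, so they no longer compare the randomised treatments cleanly. A rule that fits both 13 and 32 tests also allows different significance verdicts from the same data.

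**Working it through.** **Inputs.** Arms are 1:1 (Trial design). From Sample size calculation: "a sample size of 38 patients per group, totalling 76 patients, is required"; "efficacy in the placebo group of 10%, efficacy in the treatment group of 37"%; two-sided α 0.05; 80% power.

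**The plan's own figure.** Pooled-variance formula without continuity correction, with mean rate (0.10 + 0.37)/2 = 0.235:

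n = [1.960·√(2·0.235·0.765) + 0.842·√(0.10·0.90 + 0.37·0.63)]² / 0.27² = 37.5, rounded up to 38 per arm. The stated size is reproduced. Power at 38 per arm is 80.5% by this normal approximation and 82.3% by exact enumeration of the Pearson χ² test.

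**Size of the family.**
- Every visit tested: 9 + 8 + 8 + 6 + 1 = 32.
- One longitudinal test per score: 9 + 3 + 1 = 13.
- Instrument-visits: 8 + 8 + 6 = 22. Those after week 8: 3 scores × 3 visits (weeks 18, 39, 52) = 9.

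**First Holm threshold** (α/m): 0.05/13 = 0.00385; 0.05/32 = 0.00156.

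**First-step power**, exact Pearson χ², 38 per arm. The adverse-event rates are assumptions, since the article gives none. The efficacy row borrows the primary endpoint's planning rates.

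| Comparison | Unadjusted | m = 13 | m = 32 |
|---|---|---|---|
| AE, 50% vs 20% | 80.0% | 45.4% | 34.1% |
| AE, 30% vs 10% | 60.7% | 23.3% | 14.7% |
| Efficacy, 37% vs 10% | 82.3% | 47.5% | 35.1% |

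**Full Holm.** Later steps are easier than the first. A simulation (20,000 runs; one test with 80% unadjusted power; common correlation 0, 0.5 or 0.8; from one to m − 1 true effects) gives about 36–45% for m = 32 and 46–56% for m = 13. Relative to the 80.5% above, the loss is about 44–57% and 30–44% respectively.

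**What drives the efficacy loss.** Taking out adverse events alone (m = 32 to 31) moves first-step power only from 34.2% to 34.5% by the normal approximation, and leaves it at 35.1% by exact enumeration. Taking out the repeated visits as well, leaving 9 + 3 = 12 tests (threshold 0.05/12 = 0.00417), gives 47.5% exact.

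**The case against.** **No adverse-event test is specified.** This is correct. The article foresees descriptive reporting of the endpoints, and Holm acts only on p values that are computed. A reader might infer that harm signals are suppressed, or that a true excess must come out non-significant. The documents do not support either. Under Monitoring and Harms, all adverse events are recorded, serious events go to the review board on a fixed clock, and stopping for safety rests on the judgement of the monitoring and review boards; none of this uses an adjusted p value. Adjustment also lowers sensitivity without dictating the result. What remains is narrower: if an adverse-event p value is reported, the published sentence requires it to be adjusted.

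**The family of 32 is inferred.** This also stands. The text does not say that each visit gets its own test, and 13 fits as well, so both are shown.

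**Secondary endpoints lose most of their power.** A reader might conclude this from the first-step figure at 32 tests. It holds only at or near that step. Under full Holm at 32 tests the loss reaches half over only part of the range, and at 13 tests it does not. The article also claims no power for secondary endpoints, and strict control of them is a legitimate choice.

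**An analysis plan may define the family.** It may, and the exact make-up of the efficacy family is partly a design choice. But exempting adverse events there would depart from the rule as published, so that part is a badly drawn rule and not merely a missing detail.

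**Conclusion.** The point holds in limited form. As published, the Holm rule covers every secondary outcome, adverse events included, in a family of 13 to 32 tests. For an assumed adverse-event excess of 50% vs 20%, first-step power drops from 80% to about 45% or 34%. For a secondary efficacy endpoint with the primary's assumed effect it drops from 82% to 47.5% or 35%, and by somewhat less under full Holm.

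These sizes rest on 38 evaluable patients per arm, on adverse-event rates that the article does not give, and on an effect borrowed from the primary endpoint. The primary test and the conduct of safety monitoring are unaffected. The adverse-event part is the firmer one, because the stated rule itself errs there. The efficacy part is a matter of fixing the family before the results are seen.

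**What to change.** - State that adverse events are outside the Holm family and are reported by arm with unadjusted risk differences and 95% CIs.
- Restrict the family to the nine named binary secondary endpoints plus one week-8 contrast each for SCCAI, partial Mayo and IBD-Control, 12 tests in all. Because the article gives histological remission no time point, name one when listing it.
- Report all other visits descriptively, especially those after week 8, when open-label donor FMT may have begun.

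The cost is a sentence or two in the analysis plan, with no change to conduct or data collection. The downside is that p values at other visits are no longer confirmatory. The gain should not be oversold: with 12 tests, first-step power for a 37% vs 10% endpoint is still 47.5%, so the fix avoids the fall to 35% but keeps the price of testing 12 endpoints.

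### The responder versus non-responder microbiota regression leaves out randomised arm, which can confound it if the arms are pooled and post-FMT or change samples are used

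*Protocol article*

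**What the plan says.** The protocol article (Statistical methods) gives the purpose of the regression as "To identify microbial candidates that are associated with response to FMT" and specifies it as "comparing responders versus non-responders using linear regression analyses considering age, sex, BMI, proton pump inhibitor use, antibiotic and sequencing read depth as covariates". Six adjustment variables are named. Neither randomised arm nor donor is among them, and no other section adds them, stratifies by arm or restricts the regression to donor recipients. The section does not define a responder for this analysis, and it does not say whether baseline, post-FMT or change data enter the model. A further step follows: "Next, we will analyse data derived from the longitudinal monitoring to detect changes after FMT and donor-derived engraftment of species associated with (non)-response".

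Three other places matter:

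- **Trial design:** "Eligible patients will be randomised to receive anoxic donor FMT or anoxic autologous FMT" "in a 1:1 allocation ratio". Both arms are therefore called FMT.
- **Sample size calculation:** remission is assumed to be 10% with autologous FMT and 37% with donor FMT.
- **Investigational product:** "Patients receive FMT from the same donor for each treatment, while multiple donors are employed throughout the study".

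**The concern.** A variable that affects both sides of a comparison has to be adjusted for or stratified on. The trial's own premises give arm that role. The sample size rests on arm changing the outcome, and the Introduction and Other explorative outcomes sections expect donor FMT to change composition: engraftment is a design goal and donor strains are to be tracked. Suppose responders and non-responders from both arms are compared after treatment without arm in the model. The responder group then holds more donor recipients, and any taxon that donor material delivers will tend to be higher there, whether or not it has anything to do with response.

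What is at stake is a stated aim of the trial: to identify strains associated with response that could inform later microbial therapies. The follow-on step looks at engraftment of the species already linked to response or non-response, so it can carry a confounded list forward. Strain tracking shows where a strain came from. It does not show whether the strain relates to response once arm is held fixed.

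**Working it through.** **The plan's own figure.** The article gives no figure for the microbiota regression, so the check starts from the sample size, which supplies the rates. With p₁ = 0.10, p₂ = 0.37, mean 0.235, two-sided α = 0.05 and 80% power, using pooled variance and no continuity correction:

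n = [1.960·√(2·0.235·0.765) + 0.842·√(0.10·0.90 + 0.37·0.63)]² / 0.27² = 37.5, rounded up to 38 per group.

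This reproduces the stated 38 per group and 76 in total.

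**Arm mix of responders and non-responders.** With 1:1 allocation and remission as a proxy for response:

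- Expected responders: 38 × 0.37 = 14.1 (donor) and 38 × 0.10 = 3.8 (autologous), 17.9 in all.
- Donor-arm share of responders: 0.37 / (0.37 + 0.10) = 0.787.
- Donor-arm share of non-responders: 0.63 / (0.63 + 0.90) = 0.412.
- Difference: 0.787 − 0.412 = 0.375.

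A taxon that donor FMT shifts by d SD, with no relation to response within either arm, therefore shows an expected responder difference of 0.375·d SD when arm is left out. At the earlier trial's 20.0% versus 30.4% (Introduction), the multiplier is 0.304/0.504 − 0.696/1.496 = 0.603 − 0.465 = 0.138. With equal rates in the two arms it is 0.

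**Flag rate at p<0.05.** Simulated trials of 38 + 38 patients, with linear regression of such a taxon on response. The shift d is an assumption; the article gives none. The ranges for 37% versus 10% run from a model with six unrelated covariates (lower figure) to one with none (higher figure). The other columns have six covariates.

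| Assumed shift d | 37% v 10%, arm omitted | 37% v 10%, arm included | 30.4% v 20.0%, arm omitted | 10% v 10%, arm omitted |
|---|---|---|---|---|
| 0.5 SD | 8.7–10.1% | about 5% | 5.4% | 4.9% |
| 1 SD | 20.9–23.6% | about 5% | 7.8% | 5.2% |
| 2 SD | 47.1–50.7% | about 5% | 10.4% | 5.1% |

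**Baseline samples.** Before treatment, randomisation makes arm independent of the taxa, so d = 0 and this bias vanishes.

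**Donor, within the donor arm only.** The number of donors is not given. Assuming 4 to 12 donors and a between-donor taxon SD of 1.5, the flag rate with donor omitted is about 5% if donors do not differ in efficacy. It is 7.5–14.8% if donor efficacy varies with SD 1 on the logit scale, and 12.8–27.6% at SD 2. With donor in the model it is about 5%. Every input here except the donor-arm size and the 37% rate is assumed.

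**The case against.** The strongest reply is that the article does not state the conditions the bias needs.

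- **Sampling time.** Changes after FMT and engraftment come in a separate later step, so the listed regression may be meant for baseline samples, where this bias is absent. This stands as a limit on the claim. The article leaves the matter open, so the point has to be conditional.
- **Pooling.** Parts of the article use FMT to mean donor FMT, so the analysis could be intended for donor recipients only. Pooling is still the plainer reading, because the Trial design and Patient allocation and blinding sections call both products FMT and no restriction is given.
- **Rates.** The 37% and 10% belong to the primary endpoint of steroid-free clinical and endoscopic remission. Clinical response is a separate, looser secondary outcome with no planned rates. They are a proxy, and the 20.0% versus 30.4% column shows how far the result falls if the arms differ less.
- **Status.** The analysis is exploratory, and an article condenses a fuller protocol. However, the article does fix an adjustment list, down to read depth, and the trial's own randomised factor is not on it. That is a choice as stated and not merely a detail left out.

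A reader might infer that donor-delivered taxa will appear linked to response and dominate the candidate list. The documents do not support that: even under every condition above, a given taxon of this kind is flagged in a minority of trials at shifts of 0.5 or 1 SD and in about half at 2 SD. A reader might also take the missing donor term as an equal defect. It matters only if donors differ in efficacy. The article regards that as plausible but does not quantify it, donor has no meaning in the autologous arm, and a fixed donor term could remove between-donor signal that the trial wants to study.

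**Conclusion.** The point holds in conditional form. The stated covariate list omits randomised arm, and the article neither restricts nor stratifies the regression. If the arms are pooled and post-FMT or change data are used, a taxon delivered by donor FMT but unrelated to response within arm carries a spurious responder difference of 0.375 times its shift at the planning rates. Its false-positive rate is then roughly two to ten times the nominal 5% for shifts of 0.5 to 2 SD.

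This rests on three assumptions: remission rates standing in for response rates, assumed SD shifts, and a real difference between arms. With a smaller arm difference the inflation is slight, and with none, or with baseline samples, it disappears. Omitting donor is a secondary matter that depends on unquantified donor heterogeneity. The primary and secondary endpoints are not touched.

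**What to change.** - State which samples enter the regression (baseline, post-FMT or change), how a responder is defined for it, and whether the arms are pooled.
- In any regression on post-FMT or change data, add randomised arm as a covariate or stratify by arm.
- Report a donor-arm-only analysis as a sensitivity analysis, with donor as a random effect where the number of donors allows.
- Treat an arm × response term as exploratory only, since about 4 autologous responders are expected (38 × 0.10 = 3.8).

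Cost: no new data, because allocation and donor are already recorded. The arm term uses one degree of freedom. The donor-arm-only analysis is less precise, with about 14 responders and 24 non-responders at the planning rates, which is why it is proposed as a sensitivity analysis.
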